### Data collection and management

After patients sign the written informed consent form, scale assessments will be conducted. Each patient will have a separate folder to store their informed consent forms and completed scales. All the clinical data will be input into EpiData3.1 by two trained research assistants independently. Only the research team members have the right to access. All researchers will be trained regularly, and all data will be monitored and verified regularly by investigators throughout the trial.Due to the trial’s short duration and minimal risks, a Data Monitoring Committee will not be established. Data can be obtained by contacting the tutor after the RCT is published.

### Data analysis

A statistician will analyse the data using SPSS 26.0 software, considering a P-value < 0.05 as statistically significant. Continuous variables will be presented as mean ± standard deviation or median with interquartile range, while categorical variables will be expressed as frequency and percentage. The outcome measures in this study are all continuous variables. Differences in outcomes at baseline, week 8, and week 12 will be analysed using repeated measures ANOVA or mixed linear regression analysis. Both the intention-to-treat (ITT) and per-protocol (PP) populations will be included in the analysis. The ITT and PP analysis results will be compared to ensure consistency. In cases of missing data, the last observed value will be carried forward for interpolation. A safety analysis will be performed to assess safety outcomes.

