**Methods:**

This study is a dual-arm, single-center, single-blind, randomized controlled trial. A total of 86 AIS patients will be enrolled and randomly assigned in a 1:1 ratio to either the intervention group or the control group. The control group will receive conventional exercise education and follow-up. The intervention group first watched tactile stimulation followed by TC action videos, and then practiced imitating TC movements. The program will be implemented once a day for 30 min, 5 days a week for a duration of 8 weeks. Outcome measures will be assessed at baseline, week 8, and week 12. The primary outcome is global cognitive function and secondary outcomes are language, attention, executive function, memory, visuospatial ability, neuropsychological assessments, and quality of daily life.

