### Sample size calculation

Calculate the sample size according to the following formula:

$$n=2{\left(\mu_{\alpha }+\mu_{\beta }\right)}^{2}\sigma^{2}/\delta^{2}$$
*n* is the sample size for each group; *μ_α_* is the u value corresponding to the Type I error probability, and *μ_β_* is the u value corresponding to the Type II error probability; *δ* donates the expected effect size, i.e. the absolute value of the difference in means between the two groups, and σ^2^ is the population variance, estimated by the sample variance, which is the mean of the variances of the two groups. *α* is set at 0.05 and *β* is set at 0.10. According to Yeh et al.’s study [32], σ = 4.985, δ = 2.33, the calculated sample size for each group is 30. Considering a 25% dropout rate in previous studies [33] and the potential for a higher dropout rate in cognition-related studies [34], we increased the dropout rate to 30%. Ultimately, we determined that each group should include 43 patients.

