### Outcomes

At baseline, patients will undergo the AD8 test to screen for pre-stroke cognitive impairment; those identified with such impairment will be excluded. Routine sociodemographic data will also be collected, including age, gender, marital/cohabitation status, employment status, as well as personal and family medical history, and smoking and alcohol consumption habits.

Validated assessment tools will be employed to evaluate global cognitive function, memory, language function, executive function, attention, visuospatial ability, activities of daily living, neuropsychiatric symptoms, and psychological status. Each scale will be analysed independently, no composite total score will be calculated across different scales.

Subjects will be evaluated at three time points: before the intervention (1–2 days before the start, T1), after the intervention (1–2 days following the 8-week intervention, T2), and during follow-up (4 weeks after the 8-week intervention, T3). The safety outcome, particularly the incidence of falls, will be monitored throughout the study.

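### The MoCA analysis names no primary effect or visit and does not adjust for baseline, although the trial is sized on one difference between two means

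*Protocol article*

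**What the plan says.** All efficacy outcomes share one sentence in Data analysis: "Differences in outcomes at baseline, week 8, and week 12 will be analysed using repeated measures ANOVA or mixed linear regression analysis". P < 0.05 is the general threshold for significance. Missing values are filled by carrying the last observation forward. On populations the section says "Both the intention-to-treat (ITT) and per-protocol (PP) populations will be included in the analysis", and adds that the two sets of results will be compared for consistency.

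The abstract states "The primary outcome is global cognitive function", and the Primary outcomes section identifies this as MoCA. Neither gives a visit. The Outcomes section says "Subjects will be evaluated at three time points" (before the intervention, after its 8 weeks, and 4 weeks later) and ranks none of them.

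The Sample size calculation section uses the two-sample formula for means. Its δ is defined as "the absolute value of the difference in means between the two groups", with no visit, no repeated measurement and no correlation with baseline. The result is given as "σ = 4.985, δ = 2.33, the calculated sample size for each group is 30", raised to 43 per group for 30% dropout.

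**The concern.** The quantity that the trial is sized on is not tied to any test in the analysis section. A three-visit model offers at least three answers: the group effect averaged over visits, the group-by-time interaction, and a contrast at one visit. They estimate different things and differ in power.

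The group effect is the weak one. Randomisation makes the expected baseline difference zero, so averaging it in dilutes the effect to two thirds. The interaction avoids this, but it is a 2-df omnibus test and does not return the single difference used for sizing. A baseline-adjusted contrast targets that difference directly and uses the baseline MoCA already collected, yet the sentence does not mention adjustment.

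Two things are at stake. One is power that could be had without new data. The other is a single confirmatory test fixed before the results are known, in a trial whose participants and therapists are unblinded.

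**Working it through.** **Inputs.** From Sample size calculation: σ = 4.985, δ = 2.33, α = 0.05 (taken as two-sided), β = 0.10, 30 per group, and 43 after dropout. Assumptions not in the article: equal correlation ρ between any two visits, taken as 0.5 and 0.7; the same difference of 2.33 at weeks 8 and 12; equal SD at all visits.

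**The plan's own figure.** n = 2(1.960 + 1.282)² × 4.985² / 2.33² = 96.2, so 97 per group, not 30. The dropout step does reproduce: 30/0.7 = 42.9, so 43. The value of 30 is a separate error. It makes efficient analysis matter more, but this point does not rest on it.

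**Power of each reading, 43 per arm.** Here √(2/43) = 0.2157 and power = Φ(estimate/SE − 1.96).

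- Unadjusted comparison at one visit: SE = 4.985 × 0.2157 = 1.075; z = 2.17; power 58%.
- Contrast adjusted for baseline, SD = σ√(1 − ρ²). At ρ = 0.5: SD 4.32, SE 0.931, z = 2.50, power 71%. At ρ = 0.7: SD 3.56, SE 0.768, z = 3.03, power 86%.
- Three-visit group effect: estimate (0 + 2.33 + 2.33)/3 = 1.553, SD = σ√((1 + 2ρ)/3). At ρ = 0.5: SE 0.878, z = 1.77, power 42%. At ρ = 0.7: SE 0.962, z = 1.62, power about 36%.

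A simulation of 20,000 trials per setting, which also covers the 2-df interaction, gave:

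| Test | 43 per arm, ρ = 0.5 | 43 per arm, ρ = 0.7 | 30 per arm, ρ = 0.5 | 30 per arm, ρ = 0.7 |
|---|---|---|---|---|
| Three-visit group effect | 42% | 36% | 30% | 26% |
| Group-by-time, 2 df | 60% | 83% | 44% | 66% |
| Change from baseline to week 8 | 58% | 79% | 43% | 63% |
| Week 8 adjusted for baseline | 69% | 85% | 53% | 69% |

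A separate run of 4,000 trials, testing the interaction by Hotelling's test on change scores, gave 59% and 81% at 43 per arm. Hence the range of 59–83% for that test.

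Over a wider range of ρ the formulas give, at 43 per arm, 62% (adjusted) against 51% (group effect) at ρ = 0.3, and 95% against 34% at ρ = 0.8.

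**Two follow-up visits.** If either visit could carry the claim, the type I error is 1 − P(|Z₁| < 1.96 and |Z₂| < 1.96). For test statistics correlated 0.5, 0.7 and 0.85 (assumed), this is 9.1%, 8.4% and 7.4%.

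**The case against.** The best defence is that a journal article condenses a fuller protocol (version 2.0, not shown), and that model terms and contrasts normally sit there or in a statistical analysis plan. That excuses missing detail. It does not cover an analysis sentence that lists baseline among the outcome visits and leaves the model open, in an article that gives its primary outcome without a visit.

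A second defence is that keeping baseline as an outcome is not itself an error. This is right: a mixed model that constrains the arms to equal baseline means loses essentially nothing against covariate adjustment. The sentence states no such constraint.

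Third, the article never says that the group effect is the test. Group-by-time is at least as natural a reading, and there the gain from adjustment is modest. The low figures of 36–42% apply only if the group effect is used.

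A reader might infer more than the text supports:

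- *Repeated measures ANOVA would be a complete-case analysis.* The section fills missing values by carrying the last observation forward, so this does not follow.
- *ITT and PP are two routes to significance.* Neither is named primary, but the stated purpose of analysing both is a consistency check.
- *Any significant result counts as success.* Taking the best of group effect, interaction and two visit contrasts would give about 14% type I error, but no such rule is stated. The 7–9% is likewise conditional on an either-visit claim, which the article neither makes nor rules out.

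**Conclusion.** The point holds as a fault in how the primary analysis is fixed: an open choice of model, no named effect or visit, and no baseline adjustment, against a sample size built on one difference.

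With 43 per arm, a baseline-adjusted contrast at one visit gains about 9–10 percentage points over the group-by-time test at ρ = 0.5 and 2–4 points at ρ = 0.7. Against the three-visit group effect it gains about 27 and 49 points. With 30 completers the gains are about 9 and 3 points, and about 22 and 43 points.

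These sizes rest on the assumed correlation, on an equal effect at both follow-up visits, and on the article's own SD and difference. The finding that no primary test is fixed rests on no assumption. It should be corrected before analysis. It does not show that the trial will use its weakest option or claim success at whichever visit favours it.

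**What to change.** Delete the repeated measures ANOVA alternative and state one primary analysis, for example:

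> MoCA at weeks 8 and 12 will be analysed in the ITT population by a linear mixed model with arm, visit, arm-by-visit and baseline MoCA. The primary test is the arm contrast at [one named visit], two-sided 0.05, reported as an adjusted mean difference with 95% CI. The contrast at the other visit is secondary. The PP analysis is a consistency check.

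A mixed model on all three visits that constrains the arms to equal baseline means is an acceptable alternative. Week 8, the end of the intervention, is a natural primary visit. The abstract, however, frames the aim as long-term effects, which could equally point to week 12, so the sponsor should reconcile the two and choose. Use the same baseline-adjusted form for the secondary scales. Education should not be written in as a covariate on the present text, because the Outcomes section does not list it among the baseline variables.

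The cost is wording only: no new data and no additional patients. The sponsor gives up the choice of visit after the data are seen.

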### Eligibility criteria

#### Inclusion criteria

The first stroke was in accordance with the Chinese guidelines for diagnosis and treatment of acute ischemic stroke 2023 [31] and was confirmed by brain CT or MRI.First onset of stroke, with disease duration of less than 14 days;The NIHSS score less than 5;Muscle strength of limbs > level 3.

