The brain’s ability to reorganize itself, known as neuroplasticity, peaks immediately after stroke [55]. Timely and appropriate training and stimulation allow undamaged neurons to reconfigure their connections, compensating for functions of damaged regions and optimizing rehabilitation outcomes [56]. Existing research indicates that implementing non-routine or alternative therapies within 1 to 60 days post-stroke results in better cognitive recovery outcomes compared to homologous interventions during the chronic phase [57]. Thus, this study advances the intervention window to capitalize on the nervous system’s heightened plasticity. By administering precise treatment and stimulation during this acute period, we aim to more effectively facilitate brain reorganization and functional recovery, thereby preventing cognitive impairments or enhancing cognitive function in patients with deficits.

We anticipate that the therapeutic program described here will help AIS patients prevent the onset of cognitive impairment and improve their overall quality of life. The planned randomized controlled trial will contribute evidence on the effectiveness of integrating TC-AOT and SOT in stroke rehabilitation.

However, implementing the therapy may pose challenges such as prolonged intervention cycle and poor patient adherence. Additionally, this study is single-centered, which may limit the generalizability of this approach to other centers. Another limitation lies in participants in the intervention group received longer exposure time, which could bias the results. Furthermore, future studies should consider incorporating functional connectivity biomarkers (e.g. fNIRS, EEG) to provide more objective insights into the neural mechanisms of cognitive recovery. Multidisciplinary collaboration will be essential to achieve this goal and further advance the field of stroke rehabilitation.

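### Last observation carried forward is the only missing-data rule, so anyone lost before week 8 is analysed as unchanged from the acute-phase MoCA

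*Protocol article*

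**What the plan says.** Under Data analysis, the protocol article fixes one rule for incomplete data: "In cases of missing data, the last observed value will be carried forward for interpolation". The rule is not limited to any outcome, visit or analysis set. The same section offers repeated measures ANOVA or mixed linear regression for the three time points, and compares the intention-to-treat results with the per-protocol results.

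Three other statements bear on how the rule will act:

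- Sample size calculation: "we increased the dropout rate to 30" percent, and then "we determined that each group should include 43 patients".
- Inclusion criteria: "First onset of stroke, with disease duration of less than 14 days". The Outcomes section puts the baseline assessment 1 to 2 days before the intervention starts. The only later assessments are after the 8-week intervention and 4 weeks after that.
- Discussion: "The brain’s ability to reorganize itself, known as neuroplasticity, peaks immediately after stroke". The authors give this as a reason for starting early.

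**The concern.** With one baseline and two later visits, carrying forward has little to work with. A patient who leaves before week 8 has only the acute-phase MoCA, and that score is entered at weeks 8 and 12. A patient who leaves between weeks 8 and 12 carries the week-8 score. The first case assumes exactly zero change over two to three months after a stroke, in a trial designed on the expectation that cognition can change in that period.

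The protocol's own allowance makes the affected group large: 0.30 × 43 = 12.9, about 13 patients per arm. At stake is the primary intention-to-treat estimate for MoCA. It can be diluted. If the arms lose different proportions, it can also be moved in either direction by dropout alone. The comparison with the per-protocol set is no safeguard, because it does not vary the missing-data assumption.

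**Working it through.** **Inputs from the protocol article.** Difference 2.33 and SD 4.985 ("σ = 4.985, δ = 2.33, the calculated sample size for each group is 30"), 43 per arm, 30% dropout. The dropout step reproduces: 30 / (1 − 0.30) = 42.9, so 43. The 30 itself does not follow from the stated formula and error rates ("is set at 0.05 and *β* is set at 0.10"): 2 × (1.960 + 1.282)² × 4.985² / 2.33² = 96.2, so 97 per group two-sided. That is a separate matter, and nothing below depends on it.

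**Assumptions, because the article gives no figure.** Natural MoCA change g from 0 to 3 points; correlation 0.7 between baseline and week 8; dropout unrelated to outcome within arm; dropouts have the same treatment effect as completers; timing and split of dropout as shown.

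**Expected week-8 difference under carrying forward.** With proportions d_I and d_C lost before week 8 and a true difference Δ:

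(1 − d_I)(g + Δ) − (1 − d_C)g = (1 − d_I)Δ − (d_I − d_C)g

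*Equal loss.* The term in g vanishes.

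- All 30% lost before week 8: 0.70 × 2.33 = 1.63, which is 30% too small.
- Half of it lost before week 8: 0.85 × 2.33 = 1.98, which is 15% too small.

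*Unequal loss, all before week 8.*

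| Lost, control / intervention | Δ | g = 0 | g = 1 | g = 3 |
|---|---|---|---|---|
| 20% / 40% | 2.33 | 1.40 | 1.20 | 0.80 |
| 40% / 20% | 2.33 | 1.86 | 2.06 | 2.46 |
| 20% / 40% | 0 | 0 | −0.20 | −0.60 |
| 40% / 20% | 0 | 0 | +0.20 | +0.60 |

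**Type I error.** I simulated a baseline-adjusted week-8 comparison with 43 per arm, 20,000 trials per scenario. With no true effect and a 20%/40% split, the rejection rate is about 6% at g = 1 and 13% at g = 3, against 5% on observed data. A normal approximation agrees at g = 3: bias 0.60 / SE 0.72 = 0.83, and P(Z > 1.13) + P(Z < −2.79) is about 0.13. At g = 3 it falls to about 7% for a 25%/35% split, and to about 7% for the 20%/40% split if only half the loss is before week 8. With equal loss it is 5%.

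**Standard error, 30% lost in each arm before week 8.**

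- Observed data: 4.985 × √(1 − 0.7²) × √(2 / 30.1) = 0.92.
- Carried forward, g = 0 and Δ = 0: the baseline slope becomes 0.30 + 0.70 × 0.7 = 0.79, so the SE is 4.985 × √(1 − 0.79²) × √(2 / 43) = 0.66. It rises to 0.79 at g = 3 and Δ = 2.33.

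**Power at Δ = 2.33, same loss.** It falls from 66% at g = 0 to 53% at g = 3 under carrying forward, against about 69% on observed data.

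**The case against.** Several objections have force.

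- **The sizes rest on undocumented inputs.** The 30% is a planning allowance with no timing and no split by arm, and no MoCA recovery figure is given. This stands, so the results are ranges, and 13% type I error is near the top of them.
- **A reader might infer that type I error is inflated in any case.** It is not. That needs both unequal loss and a non-zero mean change. Unequal loss is plausible, because only the intervention arm has daily sessions with photo check-ins and the Discussion expects adherence problems. But missing a session is not missing an assessment, contact details are kept for follow-up, and the gift for completing check-ins could reduce loss in that arm.
- **A reader might infer that the protocol says cognitive recovery is greatest in these weeks.** The Discussion speaks of neuroplasticity and of early therapy doing better than late therapy. It gives no course of untreated MoCA. The equal-loss result does not need one.
- **A reader might say that the standard error is computed wrongly.** In simulation the model SE matches the actual spread of the carried-forward estimator (0.79 against 0.80 at g = 3 and Δ = 2.33). The defect is that it understates uncertainty about the true effect.
- **The 2.33 target assumes that dropouts keep the full benefit.** If they gained nothing, the true intention-to-treat effect with 30% loss in each arm would be 0.70 × 2.33 = 1.63. Carrying forward would then land on it, and an observed-data analysis would overstate it. This stands as a reason for a sensitivity analysis. It does not rescue the rule, because the term (d_I − d_C)g remains whenever loss is unequal and scores change.

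**Conclusion.** The concern holds. It is a rule stated in the current text and not a detail left to an analysis plan. Under missing at random with 30% lost in each arm, a 2.33-point MoCA difference is estimated as about 1.6 if all loss is before week 8, or about 2.0 at week 8 if half is, whatever the natural recovery.

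With unequal loss the bias can go either way. In the scenarios tried, the estimate of a true 2.33 ranges from 0.80 to 2.46. With no true effect, a 20%/40% split and 1 to 3 points of recovery, a spurious 0.2 to 0.6 points appears, with 6% to 13% type I error. With equal loss and no true effect there is no bias.

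Because carried-forward values count as observed data, the standard error (about 0.7 to 0.8 against 0.92) understates uncertainty about the true effect. Recovery, timing, split and the correlation of 0.7 are assumptions. What the documents themselves establish is the mechanism and the size of the dropout allowance.

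**What to change.** Before unblinding, change the Data analysis section as follows:

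1. Delete the sentence on carrying forward, or keep that method only as a labelled sensitivity analysis.
2. Name the mixed linear model, which the section already offers as an alternative, as the primary intention-to-treat analysis of MoCA. Fit it to all observed values without imputation. It is valid under missing at random.
3. Add one sensitivity analysis that departs from missing at random, for example multiple imputation with a shift applied to dropouts.

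Further detail, such as the covariance structure or the arm to which a shift applies, can be left to the analysis plan. The cost is slightly more analysis work and a wider, more honest standard error. Visits, patients and treatment are unaffected.

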### Monitoring

To enhance patient adherence and ensure the effectiveness of the trial, researchers will establish a rapport with patients during communication, inquiring about their level of enthusiasm for participation. Patients will be informed that after discharge, they will need to watch the training videos at home and check in using the ‘Jielong Butler’ WeChat applet. To verify the authenticity of each training session, patients will be required to upload three photos showing their ongoing training activities. These photos will be submitted by the patients’ family members and reviewed by the research team to ensure compliance. This process will also ensure that patients are accompanied by their family members during the exercises. Additionally, patients who consistently complete the check-ins for 8 weeks will receive a small gift as an incentive. After these details are communicated to the patients and their families, the written informed consent will be obtained, and the contact information of the patients and their families will be recorded for follow-up and monitoring.

Data collectors received standardized training on questionnaire evaluation, mastering the content, assessment methods, and techniques while remaining unaware of the study’s group assignments. During data collection, they refrain from guiding or suggesting responses to participants, and the intervention will not be mentioned during assessments to maintain objectivity and consistency. Two university researchers are responsible for data entry and verification to ensure accuracy.

Although the intervention is non-invasive, adverse events such as falls or fractures may occur. To ensure safety, patients and their families will be provided with staff contact information *via* phone or WeChat, and instructed to contact staff immediately if any adverse events occur. Details of all adverse events will be recorded during the trial in the case report forms (CRFs). The ethics committee will examine any connections between adverse events and the intervention and decide whether the study should continue.

